# STUDY DESIGN

In this cluster randomized controlled trial, performed in both locations of the Amsterdam University Medical Centre, we will randomize 6 surgical and 6 medical departments to either standard care group (SG) or WEsleep intervention group (WI). All adult patients admitted to the participating departments will receive the sleep improving interventions during their admission, informed consent will be obtained for sleep assessment.

Implementation of the interventions will be evaluated on a regular basis throughout the length of the study to make sure that all interventions are provided to our patients as planned. Before implementation, a baseline measurement will be conducted on all participating departments in a small number of patients (which is not part of the sample size). We observed that some interventions were gradually implemented. As such, we decided that for optimal assessment of the effect of the intervention a run-in period of 12 weeks before starting assessment of the primary and secondary outcomes would be reasonable. Sleep measurements between study onset and outcome will be used to guide implementation and will be reported in eventual journal articles.

After 12 weeks (that is, after July 1st), 33 patients per participating department will be included, for a total of 396 patients (12 departments with 33 patients each) and analyzed for the outcomes of the study. Informed consent for sleep measurements will be obtained on the first or second day of admission into one of the participating wards. Patients will be followed until discharge or for a maximum of 7 nights of admission. Patient characteristics, as well as data on the admission will be extracted from the electronic medical record. Patients will be asked to complete two questionnaires daily: Richards Campbell Sleep Questionnaire (RCSQ) on subjective sleep quality and the Consensus Sleep Diary (CSD) for day-to-day sleep wake timing. Furthermore, patients are asked at admission to complete the two questionnaires on sleep quality and sleep-wake timing on work- and work-free days (RCSQ and CSD) retrospectively, i.e. for 30 days before admission. Surgical patients will also complete a Quality of Recovery 15 (QoR-15) questionnaire twice (once at one day after surgery/first day of admission and once three days after surgery/third day of admission).

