## Randomization

As this is a cluster randomized controlled trial, patients will not be randomized individually. 12 departments will be asked to participate in the trial (6 medical and 6 surgical departments. Medical and surgical departments will be randomized separately, using a standard method of randomization (e.g. randomization.com). This will yield 3 medical en 3 surgical departments in both groups (intervention vs. control). The Intensive Care Unit and the surgical department for Cardiothoracic Surgery will be excluded from randomization. Inclusion of departments will stop when 6 medical and 6 surgical departments are found that are willing to participate.
3 medical and 3 surgical departments will provide care using the WEsleep-protocol from the start of the trial. The other departments will provide standard care during this time.

After the study, we will also implement the interventions at the control departments, as long as the preliminary results are positive.

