# STATISTICAL ANALYSIS

All patients with a total RCSQ score on the primary outcome night (second night of admission for medical patients and first night postoperatively for surgical patients) will be included in the final analysis. The baseline characteristics of all subjects, and per treatment group, will be outlined in a table describing variables such as demographic variables, weight, length, relevant medical history, current medication use, current ASA classification and type of anaesthesia. Continuous data will be presented as mean with standard deviation (SD) or as median with interquartile range (IQR), depending on the distribution of the data. Drop-outs will be replaced. Confounding will be evaluated using a linear regression analysis.

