### Sample size calculation (cfr 4.4 Sample size)

**Sample size for measuring difference in sleep quality measured by RCSQ between intervention and control group**

Sample sizes of 99 in group SG and 99 in group WG which were obtained by sampling 3 clusters with an average of 33 subjects each in group one and 3 clusters with an average of 33 subjects each in group two, achieve 80% power to detect a difference on the RCSQ between the group means of at least 7.7. We have obtained this difference from a study using RCSQ to assess the relation between sleep and delirium prevalence(23). The standard deviation of subjects is 10.27. The intracluster correlation coefficient is difficult to predict so we have chosen to be on the safe side by choosing 0.030. The coefficient of variation of cluster sizes is 0.000. A two-sided t-test was used with a significance level of 0.050. This test used degrees of freedom based on the number of clusters.

In conclusion:

Medical patients:

Intervention (WG): 99

Control group (SG): 99

Surgical patients:

Intervention (WG): 99

Control group (SG): 99

Total: 396 patients.

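### The fixed primary test uses neither the randomisation stratum nor the patient's home RCSQ, does not say whether it is pooled, and sits beside a confounding regression with no stated role

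*Protocol*

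**What the plan says.** - **Randomisation** (Protocol, Randomization): "Medical and surgical departments will be randomized separately", giving 3 intervention and 3 control departments in each stratum.
- **Primary night** (Time of main endpoint): the second night of admission for medical patients, the first night after surgery for surgical patients.
- **Primary test** (10.1 Primary study parameter): an unpaired two-sided t-test at 0.05 comparing intervention with control, or the non-parametric equivalent. It has no term for stratum, baseline or department, and the section does not say whether the strata are pooled.
- **Sample size** (4.4 and 10.1.1): worked out for one stratum, 99 v 99 in 3 v 3 departments, then applied to medical and to surgical patients for a total of 396.
- **Baseline data** (Study design): "patients are asked at admission to complete the two questionnaires on sleep quality and sleep-wake timing", covering the 30 days before admission. In addition, "Before implementation, a baseline measurement will be conducted on all participating departments in a small number of patients". In 10.2, home sleep quality is used only in a secondary paired comparison.
- **Adjustment** (10 Statistical analysis): "Confounding will be evaluated using a linear regression analysis". No covariate, decision rule or relation to the primary result is given.

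**The concern.** The design separates medical from surgical departments and measures the two groups on different kinds of night, so their mean RCSQ may well differ. An analysis that drops the stratum does not follow the randomisation. Once departments are correctly treated as the unit, any medical–surgical gap then goes into the error term. The recalled home RCSQ is a plausible predictor of RCSQ in hospital, is already collected, and is unused in the primary comparison.

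Two choices are also left open. One is whether there is a single pooled primary test or one per stratum. The other is what happens if the confounding regression disagrees with the t-test. At stake are precision and a single, unambiguous primary result.

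**Working it through.** **Inputs from the protocol (10.1.1).** "A two-sided t-test was used with a significance level of 0.050"; "achieve 80% power to detect a difference on the RCSQ between the group means of at least 7.7"; "The standard deviation of subjects is 10.27"; for the ICC, "we have chosen to be on the safe side by choosing 0.030". There are 33 patients per department and 3 v 3 departments per stratum, with cluster-based degrees of freedom. **Assumed, because the protocol gives no value:** the medical–surgical gap S, and the correlation r between home and primary-night RCSQ.

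**1. The plan's own figure.** Design effect = 1 + 32 × 0.03 = 1.96. SE = 10.27 × √(2 × 1.96/99) = 2.044. Non-centrality = 7.7/2.044 = 3.77. On 2 × (3 − 1) = 4 df the power is 80.1%, against 80% stated. The figure reproduces for one stratum alone.

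**2. Stratum in a valid pooled analysis (6 v 6 departments).** Variance of a department mean = 0.03 × 10.27² + 0.97 × 10.27²/33 = 3.16 + 3.10 = 6.26 (SD 2.50). SE of the arm difference = √(2 × 6.26/6) = 1.445.

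Allocation is 3:3 in each stratum, so omitting the stratum leaves the estimate unchanged and inflates only its error. Each arm's sum of squares gains 6 × (S/2)² = 1.5S² on 5 df, so the expected variance becomes 6.26 + 0.3S²:
- S = 5: 6.26 + 7.50 = 13.76, SE 2.14
- S = 8: 6.26 + 19.20 = 25.46, SE 2.91

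Power at a true difference of 7.7 (simulated department means for S above 0):

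| Gap S (assumed) | Stratum omitted (10 df) | Stratum included (9 df) |
|---|---|---|
| 0 | 99.8% | 99.7% |
| 5 | 96% | 99.7% |
| 8 | 77% | 99.7% |

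At a smaller true difference of 4, power is 70% v 69% with no gap and 34% v 69% with a 5-point gap.

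**3. Stratum in the test as written (patient-level, 6 v 6, simulated).** At a true difference of 4, adding the stratum alone moves power from 91% to 92% (S = 5) or from 88% to 91% (S = 10). The type I error of this test is about 12–16% without the stratum and 16–17% with it, because department is ignored. Stratifying does not repair that.

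**4. Home RCSQ.** If it explains only patient-level variance, the department-mean variance becomes 3.16 + 3.10 × (1 − r²). If it explains both levels, the whole variance is multiplied by (1 − r²).
- r = 0.3: SE ratio √(5.99/6.26) = 0.977 down to √0.91 = 0.954, a cut of about 2–5%.
- r = 0.5: SE ratio √(5.49/6.26) = 0.936 down to √0.75 = 0.866, a cut of about 6–13%.

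On the plan's 3 v 3 basis, r = 0.5 at patient level only (r² = 0.25) raises power from 80.1% to 84.7%.

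**5. Pre-implementation department mean.** This was tested as an added covariate in the stratified 6 v 6 model at a true difference of 4.55, where power without it is 80%. Baseline numbers per department are assumed, since the protocol says only that they are small. With perfectly stable department effects, power is 76% with 3 baseline patients per department, 76–77% with 5, 79% with 10 and 82% with 20. With a correlation of 0.7 between baseline and later department effects it is 75–78% throughout. With few baseline patients the lost degree of freedom and the noise outweigh the gain.

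**The case against.** **The power loss belongs to a test that the protocol does not state.** This stands. The figures in step 2 describe a department-level analysis without the stratum. A reader might infer that the plan as written wastes a large share of its power. It does not: for the patient-level test the stratum is worth about 1–3 points at a difference of 4. Step 2 shows what happens if clustering is corrected and the stratum is still left out.

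**The stratum may not be ignored at all.** The sample size treats each stratum separately. If the test is run per stratum, there is no 6 v 6 comparison to stratify. This stands as an open reading, since 10.1 does not settle it. On that reading there are two 3 v 3 primary tests, and home RCSQ is still unused.

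**Chance imbalance.** A reader might infer that medical and surgical departments could end up unequally divided between arms. They cannot, given 3:3 allocation in each stratum and 33 patients per department. Other department features can differ by chance: at ICC 0.03 the department part of the arm difference has SD √(2 × 3.16/6) = 1.03 points. Randomisation still leaves the unadjusted estimate unbiased.

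**After-the-fact adjustment.** The protocol gives no timing for the confounding regression and describes no unblinding step, so it does not show that covariates will be chosen after seeing results. It shows only that nothing in its text prevents this.

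**Covariates belong in the SAP.** A covariate list may well be there, and its absence here is no fault. The point rests on what the protocol does fix: an unadjusted test that an SAP with an adjusted primary model would contradict.

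**Home RCSQ is an imperfect baseline.** It is recalled on a ward that has already been allocated, so exposure to the ward could colour it. This stands and is met by also reporting the model without it.

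**Conclusion.** The point holds in a limited form. The protocol fixes a primary test that uses neither its own randomisation stratum nor the home RCSQ, leaves pooled or per-stratum analysis unstated, and adds a confounding regression without a role.

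In a valid pooled analysis the stratum term costs about 0.1 power point at 7.7 and about 1 point at 4 when the strata agree. It protects against a loss that depends entirely on the assumed gap: about 4 points of power at a 5-point gap and about 23 at an 8-point gap, both at 7.7. The gain from home RCSQ is modest and depends on the assumed r. All figures take the protocol's SD of 10.27 and ICC of 0.03 as given.

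The documents do not support a claim that the planned analysis is biased, or badly underpowered, for want of these terms. Ignoring clustering is the larger fault and a separate one; neither covariate corrects it.

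**What to change.** - **Primary analysis (10.1).** Replace the test with one prespecified linear mixed model: primary-night RCSQ on arm and medical/surgical stratum, with home RCSQ as covariate, a random department intercept and small-sample degrees of freedom (about 12 − 3 = 9). Say which home RCSQ is used (workday or work-free day).
- **Pooling.** State that this pooled model is the primary analysis, and reconcile that with the per-stratum sample size.
- **Home RCSQ.** Report the same model without it alongside.
- **Confounding sentence (section 10).** Recast it as a named sensitivity analysis with listed covariates.
- **Pre-implementation department measurement.** Keep it out of the primary model, and use it in a sensitivity analysis at most. It comes from few patients, and the protocol does not say that it is the RCSQ.

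**Cost.** Wording only: no new data and no more patients. The stratum takes one department-level degree of freedom. Patients without a home RCSQ will need a stated rule, which can sit in the SAP.

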## Primary study parameter

Our primary study parameter is the subjective sleep quality measured by the RCSQ on the second night of admission for medical patients or the first night postoperatively for surgical patients. These were compared between patients admitted into intervention vs. control departments. If data are distributed normally, an unpaired two sided t-test with a significance level of 0.050 will be performed to compare the sleep quality of the intervention group with the control group. If data are not normally distributed, the equivalent non-parametric test will be used.

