## Sample size calculation

**Sample size for measuring difference in sleep quality measured by RCSQ between intervention and control group**

Sample sizes of 99 in group SG and 99 in group WG which were obtained by sampling 3 clusters with an average of 33 subjects each in group one and 3 clusters with an average of 33 subjects each in group two, achieve 80% power to detect a difference on the RCSQ between the group means of at least 7.7. We have obtained this difference from Unal et al, using the RCSQ to assess the relation between sleep and delirium prevalence(23). The standard deviation of subjects is 10.27. The intracluster correlation coefficient (ICC) is difficult to predict so we selected a conservative ICC of 0.030. The coefficient of variation of cluster sizes is 0.000. A two-sided t-test was used with a significance level of 0.050. This test used degrees of freedom based on the number of clusters.

In conclusion:

Medical patients:

Intervention (WG): 99

Control group (SG): 99

Surgical patients:

Intervention (WG): 99

Control group (SG): 99

Total: 396 patients.

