## Secondary study parameter(s)

- Night-to night changes in subjective sleep quality as measured with the RCSQ. To compare this a repeated measures ANOVA will be performed.
- Difference in subjective sleep quality between hospital and at home. For this outcome, we will assess the subjective sleep quality at home retrospectively at inclusion. To compare this a paired t-test with a significance level of 0.05 will be performed.
- Diurnal phase shift of sleep-wake timing: The phase shift of sleep-wake timing will be assessed by comparing midpoint of sleep during admission with midpoint of sleep on a work-free day before admission, both measured with the Consensus Sleep Diary (CSD). For this outcome, we will assess sleep-wake timing at home retrospectively at inclusion. To compare this a paired t-test with a significance level of 0.05 will be performed.
- Night-to-night changes in sleep-wake timing: The changes in sleep-wake timing (i.e. midpoint of sleep, sleep on- and offset time, sleep duration, sleep latency & inertia and daytime napping), as measured by the CSD. To compare this a repeated measures ANOVA will be performed.
- Timing of food intake and sleep quality/timing: the association between food intake timing (i.e. first and last meal of the day and whether food was eaten after 21:00h), as measured by asking patients directly for the time of the first and last meal of the day and whether patients ate after 21:00h), and subjective sleep quality and sleep-wake timing (as measured by the Richard Campbell Sleep Questionnaire. A linear regression will be performed for food timing as continuous variable, and a logistic regression will be performed for food timing after 21.00h as dichotomous variable.
- Quality of recovery (for surgical patients) and sleep quality/timing. The association between quality of recovery (in surgical patients), as measured by the Quality-of-Recovery 15 item questionnaire (QoR-15), and subjective sleep quality and sleep-wake timing (as measured by the Richard Campbell Sleep Questionnaire and Consensus Sleep Diary respectively). The QoR-15 will be completed twice by patients. A linear regression will be performed.
- 30 day mortality, assessed by checking the medical record retrospectively 30 days after admission. This will be compared between the intervention and control group by performing a Chi-square test.

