- 30-day incidence of delirium during admission, as assessed by a physician during admission. Patients will be assessed for delirium at the request of nursing staff or if the score of the Delirium Observation Screening scale is 3 or higher. The Delirium Observation Screening scale ranges from 0 to 39, with higher scores indicating a higher chance of delirium. This incidence will be compared between the intervention and control group by performing a Chi-square test.
- 30-day incidence of surgical site infections (for surgical patients), as assessed by physicians from the department where patient is admitted during hospitalization. If the patient obtained a surgical site infection after discharge, incidence was assessed in the outpatient clinic by a physician from the department where patient was admitted. This will be compared between the intervention and control group by performing a Chi-square test.

Objective sleep substudy:

- Sleep efficiency (objectively measured) during admission. Objective sleep quality will be measured by the Dreem-3 headband, using electro-encephalography (EEG) to differentiate between wakefulness, Rapid-Eye-Movement (REM) sleep and non-REM N1, N2 and N3 sleep. The primary outcome measure will be sleep efficiency (time slept divided by time in bed spent trying to sleep), compared for patients on intervention and control departments. If data are distributed normally, an unpaired two sided t-test with a significance level of 0.050 will be performed to compare the sleep quality of the intervention group with the control group. If data are not normally distributed, the equivalent non-parametric test will be used.
- Differences in objective sleep measures of sleep-wake timing during admission. Changes in sleep-wake timing (i.e. midpoint of sleep, sleep on- and offset time, sleep duration, sleep latency & inertia) will be compared for patients on intervention and control departments. If data are distributed normally, an unpaired two sided t-test with a significance level of 0.050 will be performed to compare the sleep quality of the intervention group with the control group. If data are not normally distributed, the equivalent non-parametric test will be used.
- Night-to-night changes in objective sleep measures during admission. To compare this a repeated measures ANOVA will be performed.

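### The primary test compares patients as if independent although 12 departments are randomised; at the protocol's own ICC its type I error is about 16%, not 5%.

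*Protocol*

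**What the plan says.** The Study design section makes the department the unit of randomisation: "we will randomize 6 surgical and 6 medical departments". The Randomization section under Treatment of subjects gives the split: "This will yield 3 medical en 3 surgical departments in both groups (intervention vs. control"). The planned size is "a total of 396 patients (12 departments with 33 patients each").

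The sample size calculation (section 4.4, repeated in 10.1.1) assumes a difference of 7.7 RCSQ points, SD 10.27, ICC 0.030, and 3 clusters of 33 per arm. Of its t-test it says: "This test used degrees of freedom based on the number of clusters".

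Section 10.1 then fixes the primary analysis. The comparison is between patients in intervention and control departments, and "an unpaired two sided t-test with a significance level of 0.050 will be performed to compare the sleep quality of the intervention group" against controls. Non-normal data go to the equivalent non-parametric test, which is not named. The only regression mentioned in the introduction to section 10 is for confounding.

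Section 10.2 continues in the same way. For mortality and surgical site infection: "This will be compared between the intervention and control group by performing a Chi-square test". For delirium: "This incidence will be compared between the intervention and control group by performing a Chi-square test". Sleep efficiency and objective sleep-wake timing in the substudy get the same unpaired t-test as the primary outcome. Section 10 contains no department effect, cluster summary, cluster-robust variance or stratum term.

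**The concern.** Patients on one ward share its specialty, building, noise, staffing and routines, so their scores are correlated. The randomisation balances departments, and there are only 12 of them. A t-test on 396 patients takes its standard error from variation between patients and its degrees of freedom (394) from their number. Chance differences between wards then count as evidence for the intervention: p-values are too small and confidence intervals too narrow.

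The protocol also contradicts itself, because the trial was sized for a cluster-level test and plans a different one. The practical stake is direct. The Randomization section makes roll-out to the control departments depend on positive preliminary results, and an ineffective package would have roughly three times the nominal chance of being declared effective.

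**Working it through.** **Inputs, all from the protocol.** Cluster size m = 33; 3 departments per arm within each stratum, 6 per arm overall; ICC ρ = 0.030; SD = 10.27; difference = 7.7; cluster-size variation 0; two-sided α = 0.05.

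**1. Reproduce the stated 80% power.**
- Design effect DE = 1 + (m − 1)ρ = 1 + 32 × 0.03 = 1.96.
- SE for 99 v 99 = 10.27 × √(2 × 1.96 / 99) = 2.044.
- Noncentrality = 7.7 / 2.044 = 3.768.
- Noncentral t with df = 2 × 3 − 2 = 4: power = 0.801.

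The stated figure reproduces with an allowance for the ICC and 4 cluster degrees of freedom. With the same SE and 196 patient-level df, power would be 0.963; with clustering ignored, 0.9995. The sample size therefore rests on a cluster-level test.

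**2. Type I error of the test in section 10.1.** Under the null hypothesis the patient-level t statistic has variance of about DE rather than 1, so

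actual α = 2 × [1 − Φ(1.96 / √DE)].

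At ρ = 0.030, √DE = 1.40 and actual α = 2 × [1 − Φ(1.40)] = 0.16. The protocol calls the ICC hard to predict, so the other rows below are an assumed range.

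| ICC | DE | Actual α |
|---|---|---|
| 0.01 | 1.32 | 0.088 |
| 0.02 | 1.64 | 0.126 |
| 0.03 | 1.96 | 0.162 |
| 0.05 | 2.60 | 0.224 |
| 0.10 | 4.20 | 0.339 |

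Simulation with a normal department effect at ICC 0.03 gives 0.162 with 6 v 6 departments and 0.162 with 3 v 3. The result therefore does not depend on whether the test is pooled or run per stratum. A Mann-Whitney test, the natural reading of the fallback, gives 0.166 and 0.154.

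**3. Effect of a medical/surgical difference.** The figures above assume equal stratum means. If all 12 departments are pooled without a stratum term, a stratum difference inflates the t-test's denominator. Simulated error is then about 14 to 15% for a difference of 0.5 SD and about 12% for 1 SD.

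**4. Confidence interval width.**
- Pooled, with 9 df: 1.40 × 2.262 / 1.966 = 1.6 times the planned width.
- Per stratum, with 4 df: 1.40 × 2.776 / 1.972 = 2.0 times.

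**5. Substudy.** There are 24 patients in each of four groups and three departments per group, an average of 8 per department. Assuming exactly 8 each:
- ICC 0.03: DE = 1 + 7 × 0.03 = 1.21; simulated error 7.6%.
- ICC 0.10: DE = 1.70; simulated error 13%.

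**6. Check of the remedy.** A t-test on department means has a simulated error of 0.052 with 12 departments, adjusted for stratum (9 df), and 0.050 with 3 v 3 (4 df). Power at 7.7 points is 0.801 per stratum. Pooled, SE = 10.27 × √(2 × 1.96 / 198) = 1.445, the noncentrality is 5.33, and power is about 0.997.

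**The case against.** The strongest defence is that the sentence on cluster degrees of freedom is repeated in 10.1.1, directly beneath the primary test, and concerns a two-sided t-test at the same level. A generous reader could take the two tests as one. The protocol never uses the words patient-level or Mann-Whitney, or gives 394 degrees of freedom; these are inferred. The inference is nevertheless sound: the cluster sentence is in the past tense and describes the power calculation, while 10.1 says that patients are compared and adds no cluster term. A separate analysis plan does not answer the point either, because the protocol itself names the test and its level.

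Four qualifications stand:
- The 16% is conditional on ICC 0.030 and on similar medical and surgical means. The error exceeds 5% in every case examined with a positive ICC.
- Section 10.1 reads as one intervention-versus-control comparison, but the sample size is set per stratum. The 1.6 factor and the permutation fallback below apply to the pooled reading.
- The protocol does not fix 8 substudy patients per department; that is only the average.
- No ICC or event rate is given for mortality, delirium or infection, so the harm to the chi-square tests cannot be quantified.

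The repeated measures ANOVAs in 10.2 also carry no department term and need the same correction where they compare arms.

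**Conclusion.** The concern holds. The primary test in section 10.1 is invalid for the design and contradicts the protocol's own sample size method. At ICC 0.030 and 33 patients per department its two-sided type I error is about 16%, pooled or per stratum, assuming no medical/surgical difference; it is about 12 to 15% if the strata differ by 1 to 0.5 SD and are pooled unadjusted. Standard errors are too small by a factor of about 1.4. The non-parametric fallback does not help, and the chi-square and substudy comparisons share the defect. This must be corrected before analysis.

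**What to change.** Replace the test in section 10.1 with a linear mixed model for RCSQ on the primary night: arm and medical/surgical stratum as fixed effects, a random intercept for department, and Kenward-Roger or Satterthwaite degrees of freedom. A t-test on the 12 department means adjusted for stratum (9 df) is a simple alternative and gives nearly the same answer when departments are of equal size, as planned.

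State explicitly that the primary analysis pools the 12 departments. If it is instead run per stratum, use department means with 4 df in each.

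As the non-parametric fallback in the pooled analysis, use a permutation test over the allocations the randomisation could have produced: 20 × 20 = 400, with a smallest two-sided p of 2/400 = 0.005. Within one stratum there are only 20 allocations and the smallest p is 2/20 = 0.10, so this fallback cannot serve a per-stratum analysis.

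For mortality, delirium and surgical site infection, replace chi-square with a comparison of department-level proportions. A logistic mixed model with a small-sample correction is an option only if events are frequent enough to fit it; surgical site infection has just 6 departments. Add a random department effect to the substudy comparisons and to the repeated-measures comparisons of arms.

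The cost is analysis wording and honestly wider intervals. No extra patients or data are needed, and on the protocol's own assumptions power remains 80% per stratum and about 99.7% pooled.

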# METHODS

## Study parameters/endpoints

### Main endpoint

Our primary outcome is the subjective sleep quality as measured the Richards-campbells sleep questionnaire.

Subjective sleep quality will be assessed with the Richard Campbell Sleep Questionnaire (RCSQ). The RCSQ measures sleep quality on five questions using a visual analogue scale (VAS), ranging from 0 to 100, with higher scores indicating a better sleep quality. A sixth question was added to assess noise levels (as is quite customary), using a VAS-scale, ranging from 0-100, with a higher score indicating more noise.

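### The observed distribution chooses the primary test, although the trial is sized on a difference in mean RCSQ that the non-parametric branch need not test

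*Protocol*

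**What the plan says.** Section 10.1 (Primary study parameter) compares RCSQ on the primary night between intervention and control departments by a two-branch rule. The first branch reads "If data are distributed normally, an unpaired two sided t-test with a significance level of 0.050 will be performed". The second reads "If data are not normally distributed, the equivalent non-parametric test will be used". The section does not say how normality is to be judged, which test counts as equivalent, or what effect estimate and interval accompany either test. Section 10.2 repeats the rule for sleep efficiency, the main outcome of the objective sleep substudy, and for objective sleep-wake timing.

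The sample size sections (4.4 and 10.1.1) rest on a mean difference: 99 v 99 patients "achieve 80% power to detect a difference on the RCSQ between the group means of at least 7.7". The endpoint is bounded, "ranging from 0 to 100, with higher scores indicating a better sleep quality".

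The opening of Section 10 also lets descriptive summaries move from mean (SD) to median (IQR) with the distribution. It mentions linear regression, but only for evaluating confounding.

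**The concern.** The planning quantity is a difference in means. A rank test of the Mann-Whitney type asks whether a score from one arm tends to exceed a score from the other. The two questions coincide when the arms differ by a pure shift. They part when the intervention also changes spread or shape, which is possible on a bounded scale. The data would then decide which hypothesis the primary analysis addresses, by an unstated criterion. In the non-parametric branch no designated result could be set against the 7.7 points.

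**Working it through.** **1. The plan's own figure.** Inputs from the sample size sections:
- SD: "The standard deviation of subjects is 10.27"
- ICC: "we have chosen to be on the safe side by choosing 0.030"
- clusters in each stratum: "3 clusters with an average of 33 subjects each in group one and 3 clusters with an average of 33 subjects each in group two"
- cluster sizes: "The coefficient of variation of cluster sizes is 0.000"
- two-sided alpha 0.05, degrees of freedom taken from the number of clusters

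Design effect = 1 + (33 − 1) × 0.030 = 1.96.

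SE of the mean difference = 10.27 × √(2 × 1.96 / 99) = 2.044.

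Noncentrality = 7.7 / 2.044 = 3.768; df = 6 − 2 = 4.

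Power from the noncentral t distribution = 80.1%, and the difference detectable at 80% power is 7.69. The stated 80% is reproduced as the power of a cluster-adjusted comparison of means. With df = 196 instead of 4 the same inputs would give 96.3%, so the plan did use cluster-based degrees of freedom.

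**2. How often the switch might fire.** The documents give neither an RCSQ distribution nor a normality criterion, so everything here is assumed: beta-distributed scores on 0-100, independent patients, and a switch whenever Shapiro-Wilk gives p < 0.05 in either arm. Section 10.1 does not say whether the strata are pooled, so both sizes are shown (2 × 99 = 198 per arm if pooled).

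| Mean, SD | 198 per arm | 99 per arm |
|---|---|---|
| 60, 10.27 | 24% | 14% |
| 70, 10.27 | 81% | 48% |
| 50-70, 20 | 84-100% | about 40-100% |

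**3. What the switch changes when the means are equal.** Same score model, 198 per arm, percentage of trials with p < 0.05 on the Mann-Whitney test:

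| SDs in the two arms | Means | Rank test |
|---|---|---|
| 15 v 25 | 65-70 | 23-41% |
| 15 v 25 | 60 | about 13% |
| 15 v 25 | 50 (symmetric) | about 6% |
| 18 v 22 | 65-70 | 8-11% |
| 10.27 v 12 | 50-70 | 5-6% |
| 20 v 20 | 50-70 | about 5% |

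Welch's t-test stays at 5-6% in the SD 15 v 25 setting at means 65-70.

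A different set of assumed shapes (99 per arm, independent patients) gives the same picture:
- One arm normal, the other left-skewed, both with mean 60 and SD 10.27: t-test 5.8%, rank test 13.6%. The medians are 60.0 and 62.7 although the means are equal.
- Both arms left-skewed, SDs in ratio 1:2: t-test 5.0%, rank test 44.5%.
- The same skewed shape in both arms: t-test 4.1%, rank test 4.6%.

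**4. Is the switch needed?** With the same skewed shape in both arms, the t-test keeps its level (4.1%). With a shift of 7.7 points added, both tests reject in at least 99.8% of trials. For independent patients at this size, the non-parametric branch protects nothing that needs protecting. These runs ignore clustering, so they do not show that either test is valid in this trial.

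**5. Clustering.** Under the null with ICC 0.03 and 3 × 33 patients per arm, simulated type I error is 15.9% for the t-test, 15.4% for the rank test and 16.0% for the two-stage rule. The excess is common to both branches.

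**The case against.** The strongest reply is that the harm comes from a corner case. The protocol gives one SD, 10.27, and nothing in it suggests that spread would differ between arms. When spreads are similar, or scores symmetric, the rank test stays close to 5%. That stands: a reader might infer that the non-parametric branch inflates the error rate in general, and neither the documents nor the simulations support this.

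The switching rates depend on a rule that the protocol does not state. Normality might be judged from histograms or Q-Q plots, which would tolerate small departures. That also stands, and the rates are illustrative only. The missing criterion is, however, part of the defect.

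A reader might also infer that the trial could finish with no estimate of its planning quantity. That goes too far. The confounding regression in Section 10 could yield a mean difference as a by-product, and a Hodges-Lehmann shift could accompany a rank test if a pure shift were assumed. What remains is that the protocol designates neither as the primary result.

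Finally, it is tempting to hold against the rank test that it ignores departments and strata. The unpaired t-test as written ignores them equally, so this does not count against the switch. It is a separate and larger fault that removing the switch alone would not cure.

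Details of estimation may be left to an SAP. The two-branch rule itself is in the protocol.

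**Conclusion.** The point holds in limited form. The protocol fixes a data-dependent choice of primary test, with no criterion and no named alternative, in a trial sized on a mean difference of 7.7. The non-parametric branch answers the same question only under a pure shift. If the arms differ in location alone, little is lost. If they differ clearly in spread on a skewed scale, the rank test can be significant in roughly a quarter to two fifths of trials with equal means (SD 15 v 25, means 65-70), and in about a tenth with a milder difference (SD 18 v 22). These sizes rest on assumed score shapes and independent patients; the switching rates rest also on an assumed normality test. The change is worth making because it is cheap and takes an avoidable data-driven step out of the primary analysis.

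**What to change.** Delete the normality rule in Section 10.1 and state one primary analysis whatever the distribution: the difference in mean RCSQ between intervention and control with its 95% CI, adjusted for the medical/surgical stratum, from a department-level analysis or a mixed model with degrees of freedom based on the number of departments, as the sample size assumes. Written this way, the paragraph also deals with the clustering fault, which dropping the switch would not.

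If a distribution-free check is wanted, add a permutation test over department allocations within strata as a sensitivity analysis. With both strata combined there are 20 × 20 = 400 allocations, so the smallest two-sided p-value is 2/400 = 0.005. Within one stratum it would be 2/20 = 0.10, which could never reach 0.05.

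Make the same change for sleep efficiency in Section 10.2.

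The cost is rewriting the primary-analysis paragraph and its counterpart for the substudy. No new data are needed. The sample size and its planned power are unchanged: 99 per arm in each stratum still gives 80.1% for 7.7 points with df = 4.
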